### 8.3.9 Microbiota – Collecting faeces – Extra in this study

Parents of all preterm children in group 2a are asked to collect faeces at home at three different time points:

- First sample: 10-11 weeks post term (before the start of complementary feeding)
- Second sample: 15-16 weeks post term (after the ‘early-group’ has started complementary feeding)
- Third sample: 20-21 weeks post term (after both ‘early-group’ and ‘late-group’ have started complementary feeding)

To evaluate if the microbiota change due to the start of complementary feeding, samples before and after the start of complementary feeding will be compared. The late group will function as a ‘control group’ when analyzing the second sample, since the ‘early-group’ has already started with complementary feeding, whereas the ‘late-group’ has not yet started with complementary feeding.

Parents are asked to collect three samples of the faeces at home by using a fecal swab. The fecal swab is inserted in the stool in the diaper, and afterwards the fecal swab is transferred into a tube.

---

### 8.3.10 Dietary intake – Extra in this study

Parents of all children (preterm infants and term born infants (control group B)) are asked to complete three different diaries during the study period until the age of 2 years. The diaries will be pilot tested. Possibly, the diaries will be collected via a digital website.

- Version 1 (Milk diary): A diary about the breast- or formula milk before the start of complementary feeding.
- Version 2 (Start diary): A diary at the start of complementary feeding. Parents are asked to fill in when they give solid food for the first time, what kind of solid food they give and how much their child eats for the first time.
- Version 3 (2 day diary): A 2-day diary method: Parents will be asked to fill in the food diary during two days, of which one day in the weekend. Parents are asked to do this at the age of 6 months, 9 months, 1 year and 2 years.

### 8.4 Withdrawal of individual subjects

Subjects can leave the study at any time for any reason if they wish to do so without consequences. The investigator can decide to withdraw a subject from the study for urgent medical reasons.

If the parent(s) of the subject or the investigator have the idea that the subject doesn't want to participate (anymore) in this research project the subject will leave the study.

### 8.5 Replacement of individual subjects after withdrawal

There will be no replacement of individual subjects after withdrawal.

### 8.6 Follow-up of subjects withdrawn from treatment

There will be no follow-up of subjects withdrawn from the study. Subjects withdrawn from the study still participate in the regular follow-up scheme for prematurity offered by the treating hospital.

### 8.7 Premature termination of the study

The study will end prematurely if anything occurs, on the basis of which it appears that the disadvantages of participation may be significantly greater than was foreseen in the research proposal.

Procedures in case the study will be put on hold:

- Inclusion of new patients will stop immediately.

- 
- 951       • All participating pediatricians will receive a letter with information about the  
952       temporarily termination of the study as well as the reason for it. They will also receive  
953       the written information for their included patients.  
954  
955

---

## 9. SAFETY REPORTING

### 9.1 Section 10 WMO event

In accordance to section 10, subsection 1, of the WMO, the investigator will inform the subjects and the reviewing accredited METC if anything occurs, on the basis of which it appears that the disadvantages of participation may be significantly greater than was foreseen in the research proposal. The study will be suspended pending further review by the accredited METC, except insofar as suspension would jeopardise the subjects' health. The investigator will take care that all subjects are kept informed.

### 9.2 Adverse and serious adverse events

Adverse events are defined as any undesirable experience occurring to a subject during a clinical trial, whether or not considered related to the study. All adverse events reported spontaneously by the subject or observed by the investigator or his staff will be recorded.

A serious adverse event is any untoward medical occurrence or effect that at any dose results in death;

- is life threatening (at the time of the event);
- requires hospitalisation or prolongation of existing inpatients' hospitalisation;
- results in persistent or significant disability or incapacity;
- is a new event of the trial likely to affect the safety of the subjects.

All SAEs will be reported to the accredited METC that approved the protocol, according to the requirements of that METC.

Suspected unexpected serious adverse reactions (SUSARs) are defined as an adverse reaction that is both unexpected and also meets the definition of a serious adverse event (SAE). It is classified as unexpected if its nature and severity are not consistent with the product information. Since this randomized controlled trial does not use any form of drug or test product the risk of a SUSAR is very unlikely.

### 9.3 Follow-up of adverse events

All adverse events will be followed until they have abated, or until a stable situation has been reached. Depending on the event, follow up may require additional tests or medical procedures as indicated, and/or referral to the general physician or a medical specialist.

---

#### 9.4 Data Safety Monitoring Board (DSMB)

A DSMB is not needed for the SPOON-study, but is deemed to be appropriate. The composition of the committee and independent members are as follows:

- Clinical expert: dr. [name], working at Erasmus MC, Sophia, no conflict of interest with the sponsor
- Statisticus: prof. dr. [name], working at AMC Amsterdam, biostatistics, no conflict of interest with the sponsor
- Member of the “Vereniging van Ouders van Couveusekinderen” no conflict of interest with the sponsor

The reason for establishing this committee is to surveillance the ongoing safety and to perform interim analyses.

The interim analyses are planned as followed:

- When the primary outcome of 50 children is collected
- When the primary outcome of 100 children is collected
- When the primary outcome of 300 children is collected

The DSMB will assess data integrity and adverse events once every year, starting after randomization of 100 patients. The DSMB will advise the investigators if the study needs to be modified or prematurely terminated.

---

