### 3. STUDY DESIGN

The study comprises a multicenter randomized parallel group open-label controlled intervention study in which premature born children will be randomized to receive complementary feeding at the corrected age of 12 weeks (intervention group) or at the corrected age of 17 weeks (control group). The pattern and structure of the complementary feeding will be according to the advice of the well baby clinics in the Netherlands, using a standardized nutrition schedule.

Stratification will take place according to center. In order to keep the number of subjects in the different groups closely balanced at all times block randomisation will be used. According to Altman the block size used is a multiple of the number of treatments. A blocked randomization schedule, using blocks of four, will be used. The randomisation will be computer generated by Castor edc. The research is funded by Nutricia Nederland. Nutricia Nederland will have no financial interest in this study, will not delivery food products, will not have veto in how publication of results will be. In case of any disagreement regarding publication of the data, the principal investigators ([name]) of the research will make the final decision. All data analysis will be supervised by the principal investigators.

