## 10. STATISTICAL ANALYSIS

Since the sample size was not archived, the data will be interpreted with caution. Data will be analyzed on an intention to treat basis. In addition, we will also perform a per protocol analysis, taking into account the attrition rate. In case of missing values we will use multiple imputation. For the per protocol analysis, the criteria for the start of complementary feeding will be 12-13 weeks for the early group and 16-17 weeks for the late group. A p-value of 5% will be regarded as statistically significant and results will be presented with 95% confidence intervals.

Categorical data will be presented in absolute numbers and percentages. If a metric variable is normally distributed results will be shown in mean and standard deviation (sd). If a metric variable is not normally distributed median will be used with the interquartile range.

Descriptive data on BMI will be compared with the most recent Dutch growth chart. For the primary study parameter, the prevalence of obesity, the percentage of patients that develop overweight by using the IOTF will be calculated and intervention group and control will be compared including prevalence ratios with 95% confidence intervals. Furthermore, BMI and BMI z-scores between the intervention and control group will be compared as continuous variables.

The results of the questionnaires (BEBQ, CFQ, ITQoL / PedsQL, ASQ) will be analysed according to the scoring tables attached to the questionnaires. Allergy will be scored by a SCORAD form and can be presented as continuous or categorical variable. All blood and faeces results will be analysed as continuous or categorical variable. The diary results will be analysed as a continuous variable.

For all sub-objectives (as formulated in chapter 2), the intervention group and control group will be compared to determine the effect of early versus late introduction of complementary food, using a independent t-test or nonparametric test. For subgroup analysis, i.e. for children with respiratory problems or tube feeding, logistic regression will be used.

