### 12.2 Monitoring and Quality Assurance

During this study, there is no use of a Data Safely Monitory Board. The risks associated with this study are minimal. The intervention of this study, namely the introduction of complementary feeding, will only be guided by giving advice of how to introduce solid foods.

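### Three interim analyses of the primary outcome are scheduled with no threshold of their own beside a single 5% level, and another section says there is no monitoring board

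*Protocol*

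**What the plan says.** Protocol Section 9.4 composes a three-member board and gives its purpose: "The reason for establishing this committee is to surveillance the ongoing safety and to perform interim analyses". It lists three analyses, each triggered by a count of children whose main endpoint is available. The first is due "When the primary outcome of 50 children is collected"; the second and third follow the same pattern at 100 and 300.

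A yearly review of data integrity and adverse events, starting after 100 randomisations, is listed separately. On consequences, the section says: "The DSMB will advise the investigators if the study needs to be modified or prematurely terminated". It does not say what is compared at each look, with which test, or at what level.

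Section 10 gives one threshold, "A p-value of 5% will be regarded as statistically significant", with 95% confidence intervals, and does not mention interim looks. Section 4.3 computes 275 children per group at a significance level of 0.05 and 80% power, then 579 in total after 5% loss, rounded to 600.

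Section 12.2 states: "During this study, there is no use of a Data Safely Monitory Board".

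**The concern.** Two things do not fit together.

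First, 9.4 and 12.2 cannot both be true. A reader cannot tell whether a board existed, and so whether the interim analyses assigned to it took place.

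Second, the protocol fixes the number, timing, endpoint and possible consequence of the looks, and beside them states one unadjusted 5% level and a sample size that uses all of it. If that level were applied at every look, it would not be the overall error rate. The first look also carries very little information, so a difference of a few children could bear on advice to modify or stop.

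This matters more because Section 10 reports that the planned sample size was not reached. Readers of the results will want to know whether any interim comparison influenced the trial's course.

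**Working it through.** **1. The plan's own figure.** Inputs from Section 4.3: 6% versus 13%, alpha 0.05, power 80%, loss 5%. With pooled proportion 0.095, the two-sided formula without continuity correction is

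n = [1.960·√(2·0.095·0.905) + 0.842·√(0.06·0.94 + 0.13·0.87)]² / 0.07² = 274.2, so 275 per group.

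Then 550 / 0.95 = 578.9, so 579. Both stated figures reproduce. A one-sided calculation would give 216, so the 5% is two-sided. Nothing is set aside for interim testing.

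**2. Overall type I error if every look used two-sided 5%.** Under the null, the test statistics at looks with n_i < n_j children have correlation √(n_i/n_j); for 50 and 100 this is √0.5 = 0.71. The overall error is 1 − P(|Z| < 1.96 at all looks), from the multivariate normal distribution. Section 10 gives no achieved sample size, so the final N is an assumption, shown over a range.

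| Looks tested at 5% | Final N | Overall error |
|---|---|---|
| 50, 100, 300, final | 550 | 14.7% |
| 50, 100, 300, final | 600 | 14.8% |
| 50, 100, 300, final | 500 | 14.5% |
| 50, 100, 300, final | 400 | 13.9% |
| 50, 100, 300, final | 320 | 12.9% |
| 300, final only | 600 | 8.3% |

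If fewer than 300 children are measured, the third look never occurs and this table does not apply.

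**3. Check with binary data.** Simulation with the same prevalence in both arms, looks at 50, 100 and 300, final N 600, 400,000 runs:

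| Prevalence | Pearson test |
|---|---|
| 6% | 13.0% |
| 8% | 14.0% |
| 9.5% | 14.7% |
| 13% | 15.6% |

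With Fisher's exact test the range over the same prevalences is 5.8% to 8.7%, because that test is very conservative when events are few.

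**4. Information at the first look.** With 25 per arm, expected overweight children are 25 × 0.06 = 1.5 and 25 × 0.13 = 3.25. A split of 0 versus 4 gives Pearson p = 0.037 but Fisher p = 0.11. Fisher's test first falls below 0.05 at 0 versus 6 (p = 0.022); 0 versus 5 gives 0.0502.

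**5. What a strict boundary would do.** With p<0.001 (|Z| > 3.29) at 50, 100 and 300 and 5% at the end, the overall error at final N 600 is 5.2%. Solving for the final critical value that holds exactly 5% gives |Z| > 1.974, a nominal level of about 0.048, at final N of 550 or 600.

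**The case against.** The strongest reply is that the protocol nowhere says each look is tested at 5%. Section 10 presents 5% as the significance level of the analysis and never mentions the looks. Section 9.4 says when the looks happen but not what is tested, and the board's role is advisory. Stopping boundaries are often placed in a statistical analysis plan or a board charter, neither of which is at hand, and the board includes an independent statistician who could hold such a rule. The size of the inflation also depends on the test, and Section 10 names none for the primary comparison. The Summary says the result will be interpreted as an association, and Section 10 asks for caution.

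Most of this stands, and it limits the point in three ways:

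- A reader might infer that 5% at each of four looks is the trial's rule and that its false-positive rate is therefore 13-15%. The documents do not support that as a statement of fact.
- A reader might take the sentence in Section 3, "All data analysis will be supervised by the principal investigators", as showing that investigators see the interim comparison. It closes a paragraph on the funder's lack of influence and does not address interim access, while 9.4 gives the interim analyses to the committee itself.
- A missing boundary alone would not be a finding against a protocol.

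Two things remain. No unseen document removes the contradiction between 9.4 and 12.2. And the protocol is not silent on the looks: it ties them to primary-outcome counts, lists them apart from the safety review, and places beside them a single threshold and a full-alpha sample size. A boundary held elsewhere would still have to be made consistent with these sections.

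**Conclusion.** The point holds in a conditional form and should be fixed. It is not shown to invalidate the trial.

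Certain from the text: 9.4 and 12.2 contradict each other, and neither the 5% level nor the sample size makes any allowance for three scheduled looks at the primary outcome.

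Conditional: if each look were tested at two-sided 5% and a significant result could be acted on or claimed, the overall type I error would be up to about 13-15% (normal theory or Pearson test, final N assumed between 320 and 600), or about 6-9% with Fisher's exact test (final N 600). If the looks involve no between-arm test of the primary outcome, they cause no inflation of this kind. With a strict boundary, it is negligible.

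**What to change.** 1. Reconcile Section 9.4 with Section 12.2: state whether the board exists and whether the interim analyses are its task.
2. State the purpose of the 50, 100 and 300 looks, in one of two ways:
   - (a) they are for safety and data integrity only, with no between-arm test of BMI or overweight; or
   - (b) a strict interim boundary applies, such as Haybittle-Peto: p<0.001 at each interim and 5% at the end (about 5.2% overall), or a final level of about 0.048 to hold 5% exactly.
3. State that unblinded between-arm interim results stay with the board.
4. If unadjusted looks have already taken place, report when they took place, what was compared and what followed.

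The cost is about one paragraph. Option (a) costs no power. For option (b) with a final level near 0.048, the critical value rises by about 0.014. Multiplied by the normal density at 0.84 (about 0.28), this lowers power at 275 per group by about 0.4 percentage points, from 80.1% to about 79.7%. With the final level left at 5%, no power is lost.

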## 10. STATISTICAL ANALYSIS

Since the sample size was not archived, the data will be interpreted with caution. Data will be analyzed on an intention to treat basis. In addition, we will also perform a per protocol analysis, taking into account the attrition rate. In case of missing values we will use multiple imputation. For the per protocol analysis, the criteria for the start of complementary feeding will be 12-13 weeks for the early group and 16-17 weeks for the late group. A p-value of 5% will be regarded as statistically significant and results will be presented with 95% confidence intervals.

Categorical data will be presented in absolute numbers and percentages. If a metric variable is normally distributed results will be shown in mean and standard deviation (sd). If a metric variable is not normally distributed median will be used with the interquartile range.

Descriptive data on BMI will be compared with the most recent Dutch growth chart. For the primary study parameter, the prevalence of obesity, the percentage of patients that develop overweight by using the IOTF will be calculated and intervention group and control will be compared including prevalence ratios with 95% confidence intervals. Furthermore, BMI and BMI z-scores between the intervention and control group will be compared as continuous variables.

The results of the questionnaires (BEBQ, CFQ, ITQoL / PedsQL, ASQ) will be analysed according to the scoring tables attached to the questionnaires. Allergy will be scored by a SCORAD form and can be presented as continuous or categorical variable. All blood and faeces results will be analysed as continuous or categorical variable. The diary results will be analysed as a continuous variable.

For all sub-objectives (as formulated in chapter 2), the intervention group and control group will be compared to determine the effect of early versus late introduction of complementary food, using a independent t-test or nonparametric test. For subgroup analysis, i.e. for children with respiratory problems or tube feeding, logistic regression will be used.

For control group B, the preterm infants will be compared with the term infants to determine the difference of growth parameters, BEBQ results and food diaries before the start of complementary feeding, at 1 year and at 2 years of age. Growth parameters and BEBQ will be presented as continuous parameters (mean and sd or median with interquartile range). The growth parameters will be compared with the most recent Dutch growth curves. For the analyses, a t-test or nonparametric test will be used.

To take into account repeated measurement on the infants (non)linear mixed models will be used with infant as random factor and treatment (intervention, control), time and

time\*treatment as fixed factors. Infant and hospital will be added as random intercept. Random slopes will be added for time dependent variables.

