## SUMMARY

**Rationale:** optimal timing of introduction of complementary feeding during infancy is necessary for both nutritional and developmental reasons. Limited evidence is available about the optimal age of solid food introduction in preterm infants and implications for both short and long term health.

**Objective:** to analyze the effect of early (12 weeks corrected age) versus late (17 weeks corrected age) introduction of complementary feeding on obesity at the age of 2 years in preterm infants.

**Study design:** the study comprises a randomized parallel group open-label controlled intervention study in which premature born children will be randomized to receive complementary feeding at the corrected age of 12 weeks or at the corrected age of 17 weeks.

**Study population:** preterm infants born between 30 and 35  $\frac{6}{7}$  weeks gestational age.

**Intervention:** the intervention group will start complementary feeding at 12 weeks corrected age. The control group will start complementary feeding at the corrected age of 17 weeks. The pattern and structure of the complementary feeding will be according to the advice of the well baby clinics in the Netherlands.

**Main study parameter/endpoint:** the main study parameter is the prevalence of obesity at the age of 2 years determined by BMI-score, according to the IOTF cut-off values and will be interpreted as association.

**Nature and extent of the burden and risks associated with participation, benefit and group relatedness:** the risks associated with this study are minimal. There will be no benefit for the individual participating in this study. To determine correlations between height, weight, BMI, and eating behaviour in preterm infants it is important to perform this study in this age category.

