### 4.3 Sample size calculation

The sample size calculation for this study is based on previous reported effects. In a population based study Jingxiong et al reported that introduction of complementary feeding before the age of 4 months resulted in a 76% higher odds in developing overweight than children introduced to complementary feeding after 4 months. Overweight in this study was defined as weight-for-length/height  $\geq 2$ SD above the median of the WHO reference for sex, i.e. weight-for-length/height z-score  $\geq 2$ SD. A study by Young et al reported that excess weight gain (defined as gaining  $\geq 0.5$  in weight-for-age Z-score) between 4 to 6 months was associated with an odds ratio of 2.5 for overweight at 18-24 months. This led to the conclusion that rapid early weight gain, for example due to early weaning, could result in obesity since known post-natal risk factors for obesity are rapid early weight gain and early weaning. Based on these studies we expect that the introduction of early complementary feeding in children will result in a higher prevalence of overweight children at the age of 2 year in comparison to later introduction of complementary feeding. Based on the given odds ratio of 1.76 and 2.5 an odds ratio of 2.3 was used to calculate our sample size. In 2009, the prevalence of overweight was 8% in two year old children in the Netherlands. Overweight was determined by measuring the BMI. BMI was calculated as weight/height and expressed as kg/m^2. Overweight and obesity prevalence rates were calculated using International Obesity Task Force (IOTF) cut-of values. In this study, the same calculation and definition will be used. Information of the prevalence of overweight in premature infants is lacking. Bocca-Tjeertes et al has shown that preterm infants are a growth restraint compared to term infants. On the other hand, Euser et al found a greater fat mass normalized for weight in preterm infants. Given this contrasting information on preterm infants, a slightly lower prevalence of overweight of 6% was used to calculate the sample size. Using the odds ratio of 2.3, the intervention group will have a prevalence of overweight of 13%. With a 0.05 significance level and a power of 80% a minimal sample size of 275 patients per group is required to detect a significant increase in the prevalence of overweight. Loss to follow-up is

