calculated to be 5%. This is based on the fact that 95% of all the infants attend the well baby clinics in the Netherlands. In case patients will not attend the hospital visits, the well baby clinics will be contacted for information about height and weight. This means that 579 children have to be included in the study, finalized by a number of 600 children.

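### Section 10 says the planned sample size was not reached, but 275 per group, 600 in total and 80% power remain the protocol's only figures

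*Protocol*

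**What the plan says.** Three places in the protocol bear on this.

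- **Section 4.3 (sample size).** For the control rate, "a slightly lower prevalence of overweight of 6% was used to calculate the sample size". For the effect, "Based on the given odds ratio of 1.76 and 2.5 an odds ratio of 2.3 was used to calculate our sample size", after which "the intervention group will have a prevalence of overweight of 13"%. The conclusion is "With a 0.05 significance level and a power of 80% a minimal sample size of 275 patients per group is required", and after 5% loss to follow-up, "This means that 579 children have to be included in the study, finalized by a number of 600 children".
- **Section 10 (statistical analysis), first sentence.** "Since the sample size was not archived, the data will be interpreted with caution". The section gives no number randomised or evaluable, no revised power and no detectable difference. It does plan an intention-to-treat analysis and, for the primary parameter, prevalence ratios with 95% confidence intervals.
- **Summary, main endpoint.** The prevalence at 2 years "will be interpreted as association". The objectives in the Summary and in section 2 still speak of the effect of early versus late introduction.

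**The concern.** Section 10 was updated to report a shortfall and section 4.3 was not. A reader who wants the trial's size and power finds only 275 per group, 600 and 80%, which section 10 says were not delivered.

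What is at stake is how a non-significant result would be read. The question is whether earlier complementary feeding raises overweight in preterm infants. Set against a retained 80%, a null result could pass as evidence that earlier feeding does no harm, when the trial may have had little chance of showing the planned difference.

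The two stated responses, caution and an associational reading, do not help. Caution tells nobody how to read the interval. The associational reading does not follow from a shortfall: fewer infants cost precision, but the contrast between randomised groups remains an estimate of effect.

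**Working it through.** **Inputs (section 4.3 unless noted).** Control prevalence p1 = 6%. Early-arm prevalence p2 = 13%. Alpha 0.05, power 80%, loss 5%. Allocation is 1:1 (section 8.2). Sidedness is not stated; two-sided reproduces the plan's figure, while one-sided would give 216 per group.

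**1. Reproduce the plan.** With mean prevalence p̄ = 0.095:

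n = [1.96·√(2p̄(1−p̄)) + 0.8416·√(p1(1−p1) + p2(1−p2))]² / (p2−p1)²

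= (0.8127 + 0.3465)² / 0.07² = 274.2, so 275 per group.

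2 × 275 / 0.95 = 578.9, so 579. Both figures match.

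**2. Power at 6% versus 13% by evaluable infants per arm.** The number reached is not in the document, so these sizes are assumptions.

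Power = Φ{[(p2−p1)·√n − 0.8127] / 0.4117}

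At n = 150: (0.07 × 12.247 − 0.8127) / 0.4117 = 0.108, so power is 54%.

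| Evaluable per arm | Power, 6% vs 13% | Early-arm prevalence detectable with 80% power |
|---|---|---|
| 100 | 39% | 19.0% (OR 3.7) |
| 150 | 54% | 16.1% (OR 3.0) |
| 200 | 67% | 14.5% (OR 2.65) |
| 250 | 76% | 13.4% (OR 2.4) |
| 275 | 80% | 13.0% (OR 2.3) |

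The last column solves the same power formula for p2 with p1 held at 6%.

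**3. Sensitivity to the smaller odds ratio in 4.3.** OR 1.76 on 6%: odds 0.06383 × 1.76 = 0.1123, so p2 = 10.1% and the prevalence ratio is 10.1/6 = 1.68. Power is 19% at 100 per arm, 26% at 150, 32% at 200, 39% at 250, 42% at 275 and 45% at 300. For 80% power, n = 690.2, so 691 per arm.

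**4. What a null result could exclude.** Suppose 6% is observed in both arms, so the prevalence ratio is 1. Then SE(log ratio) = √[2 × 0.94 / (0.06n)], and the upper 95% limit is exp(1.96·SE).

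- n = 150: SE 0.457, upper limit 2.45.
- n = 250: SE √(1.88/15) = 0.354, upper limit 2.00.
- n = 275: SE 0.338, upper limit 1.94.

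Even at the full planned size, a perfectly null result would be compatible with a ratio of 1.68.

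**Limit of these figures.** They treat infants as independent. Section 8.2 assigns the second twin to the first twin's group, so outcomes within pairs are likely to be correlated and the power figures are somewhat optimistic. The share of twins is not given, so I have not adjusted for it.

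**The case against.** The strongest reply is that section 4.3 is an a priori calculation and makes no claim about what the trial achieved, that section 10 discloses the shortfall openly, and that the confidence interval will show the precision whatever the power statement says. Much of this stands. The original calculation should be kept, and power computed from observed results would add nothing. But 4.3 is not labelled as superseded, and the number that would let a reader judge the shortfall is nowhere given.

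Four stronger readings are tempting, and the document does not support them.

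- **That 4.3 contains an arithmetic error.** OR 2.3 on 6% gives 12.8%, not 13%, and 288 per group instead of 275. This is rounding to a whole per cent, and enrolling 600 absorbs it: 600 × 0.95 / 2 = 285 per arm, with 79.6% power at 12.8%.
- **That OR 2.3 is untenable.** The 2.5 behind it concerns excess weight gain between 4 and 6 months, not feeding timing, and 2.3 exceeds the mean of the two sources, (1.76 + 2.5)/2 = 2.13. But 4.3 states what each figure measures, gives the assumed link through early weight gain, and never calls 2.3 an average. Nor is 1.76 the protocol's only timing estimate: section 1.1.2 cites a six-fold increase in obesity risk at age 3 with solids before 4 months. The 1.76 also rests on another definition of overweight. It belongs in a sensitivity analysis; it does not replace the planning value.
- **That the trial is known to be badly underpowered.** If the miss was only against 600 and at least 550 children are evaluable, power at 6% versus 13% is still about 80%.
- **That the causal reading has been abandoned.** The associational wording is one phrase in the Summary. The objectives and section 10 still describe an effect in randomised groups.

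**Conclusion.** The point holds as an inconsistency within the protocol. Section 10 says the sample size was not reached, and the only size and power on record are the ones not reached. The calculation in 4.3 is sound for its inputs and is not at fault.

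How much power was lost cannot be settled from the document. For the planned difference it runs from 39% at 100 evaluable per arm to 80% at 275. At OR 1.76 it is 42% even at 275. These figures rest on reading *archived* as *achieved*, on two-sided testing, on a 6% control prevalence and on independent infants.

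The associational wording is a smaller, separate fault: it contradicts the protocol's own objective and randomised design, and a shortfall gives no reason for it.

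**What to change.** 1. **Section 10:** correct *archived* to *achieved*. State the numbers randomised and evaluable per arm, with the smallest detectable difference or expected confidence-interval width at that number, for OR 2.3 and, as a sensitivity, OR 1.76.
2. **Section 4.3:** keep the calculation and label it as the original plan, with a pointer to section 10.
3. **Summary:** delete the associational wording. Report the already planned intention-to-treat prevalence ratio with its 95% confidence interval as the randomised effect estimate, and add the risk difference with its interval.
4. **Interpretation:** state that a non-significant result is not evidence of no increase and is to be read from the confidence interval.

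The planned ratio 13%/6% = 2.17 should not become a margin for claiming no relevant increase. A superiority planning effect is not such a margin. At 250 per arm, a null result has an upper limit of 2.00 and would pass it, although the ratio of 1.68 implied by OR 1.76 lies inside the interval.

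The cost is a few sentences and one short calculation. It needs no extra infants and no change in conduct. The downside is that the stated power becomes less favourable.
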